### Case-control study: predicting recruitment at patient level

In a case control-study nested in this cohort we will interview patients who refused or consented participation in a set of clinical trials, to identify factors which influenced the decision to participate.

We will perform qualitative semi-structured interviews. The interviews will start with open questions on the motivation of a patient to consent or refuse participation. Subsequently, the interview will be guided by a topic list that is based on the literature and on input from experienced trialists. Topics will include counselling, clarity and understanding of patient information, knowledge of and attitude towards scientific research [9,17], attitude towards the doctor or health care organisation, type of intervention, practical considerations and organisational issues, (perceived) personal benefit, (dis)trust and their social demographic characteristics. This topic list will be tailored during the study.

We will interview patients who were recently counselled for participation in a RCT in a broad range of trials in the field of obstetrics, subfertility, gynaecology, internal medicine, neurology and surgery. Patients will be selected using purposive sampling. We will interview patients from different doctors, different natures of disease, different levels of education, and different regions in the Netherlands. The number of patients to be interviewed will be dependent on the variety of responses until saturation of the data is reached. We expect this to be about 10 patients who participated and 10 patients who refused for the first subspecialty obstetrics. As we assume that reasons for the decision about participation share common components across specialties, we can complete the reasons with a smaller sample of patients from other clinical specialties. This will provide us information about the full spectrum of barriers and facilitators for participation.

Based on these barriers and motivators observed in the interviews we will construct a questionnaire to quantify these findings in a representative sample of patients in the fields of obstetrics and gynaecology, neurology, surgery and internal medicine.

### Cohort study 2: Predicting recruitment success of trials registered in the Netherlands Trial Register

In a second cohort study, we will include study trials that have been registered prospectively in the Netherlands Trial Register. The cohort of studies will consist of all studies that registered their stop date between January 1^st ^2005 and January 1^st^, 2010 (expected number of available trials N≈1000). Using a questionnaire survey, we will investigate whether issues on hospital organization, trial organization, planning and trial design are predictive for successful recruitment, defined as ≥80% of the patients recruited within the time frame defined in the grant application.

As potential predictors we will take into account trial characteristics, i.e. placebo arm, blinding, experimental status of the intervention to be evaluated; characteristics of the trial organisation, i.e. research staff available to counsel patients and acquire follow up data, who is responsible for recruitment; and characteristics of the principal investigator and the research group, i.e. composition of different expertise, experience and training in trial research. For reliable prediction modelling experts recommend that there should be at least about 10 events in the data set for each potential predictor to be included in the model [16]. In a sample of 1000 studies, with a (low) recruitment rate of 30% about 30 potential predictors can be tested reliably.

Missing values will be imputed. Like in the cohort study I, the predictive accuracy of the model will be assessed using calibration, which evaluates the correspondence between the model's predicted probabilities of recruitment success and the observed recruitment success over groups. The discriminative ability of the prognostic model will be assessed by using receiver operating characteristics (ROC) analysis.

We will perform internal validation using bootstrapping and apply shrinkage to correct for over fit.

A prediction rule will be derived from the regression coefficients of the independent predictors in the multivariable prognostic model. If a valid prediction rule cannot be constructed, we will use the model to identify risk factors for a low recruitment percentage.

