**22**	PORTRET	Women with stress incontinence aged 35-80 years	400

**23**	CUPIDO	Women with vaginal prolaps	114

**24**	Pompoen	Women with postmenopausal bleeding	200

Based on these data, we will construct a prediction model. The primary outcome will be the percentage of eligible patients recruited, defined as the number of randomized patients per centre divided by the number of eligible patients. Secondary outcomes will be the number of randomized patients divided by the number of available patients per centre stratified per study. The number of eligible patients is registered for a part of the studies and will be estimated based on the LVR, the Dutch national perinatal registry.

As potential predictors we will take into account characteristics of the clinicians, e.g. the proportion of doctors with a PhD, as well as clinicians' views on the trial, e.g. prior belief in the relevance and quality of the study design. We will also collect characteristics of the study organisation: e.g. status of the hospital (academic, teaching or general), availability of research nurses or employees for counselling of the studies, clarity of research protocol and logistics, responsibilities for recruitment. These potential predictors reflect clinicians' views on these topics, aggregated at the level of department.

For reliable modelling on prediction experts recommend that there should be at least about 10 events in the data set for each potential predictor to be included in the model [16]. As we expect a response in about 65 of 70 centres, prediction models can include about 6-7 predictors at centre level.

Missing values will be imputed. The predictive accuracy of the model will be assessed using calibration, which evaluates the correspondence between the model's predicted percentage of randomized patients and the observed percentage of randomized patients. The discriminative ability of the prognostic model will be assessed by using receiver operating characteristics (ROC) analysis. We will then perform internal validation using bootstrapping and apply shrinkage to correct for over fit. A simplified prediction rule will be derived from the regression coefficients of the independent predictors in the multivariable model. If a valid prediction rule cannot be constructed, we will use the multivariable model to identify risk factors for a low recruitment percentage.

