Interviewing patients from different specialties and trials will provide a broad spectrum of why patients participate or refuse. This will limit the number of patients interviewed from one trial, but the quantification of these reasons in a representative group of patients will allow us to examine differences between these specialties and trials.

Finally, as this study will be performed in the Netherlands, the Dutch health care system as well as the position of medical research in the Netherlands might influence its results. Existing literature can be used to compare our results with those from other countries. We realize that especially to make this study a success we need a high response rate to avoid selection of highly motivated researchers, patients and clinicians.

In conclusion, this design allows us to identify determinants for unsuccessful recruitment. Identified predictors for unsuccessful recruitment can be coupled to evidence-based strategies to improve recruitment in trials [7].

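### Cohort 2's capacity of about 30 predictors is counted on all available register trials rather than expected questionnaire returns, so at the stated 30% success rate it holds only with complete response

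*Protocol article*

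**What the plan says.** The section on cohort study 2 takes all trials in the Netherlands Trial Register with a stop date in a five-year window and gives the size of that frame as "expected number of available trials N≈1000". The data come from a survey: "Using a questionnaire survey, we will investigate whether issues on hospital organization, trial organization, planning and trial design are predictive for successful recruitment". Success is "defined as ≥80% of the patients recruited within the time frame defined in the grant application". The section cites a rule of at least about 10 events per potential predictor and concludes: "In a sample of 1000 studies, with a (low) recruitment rate of 30% about 30 potential predictors can be tested reliably". It gives no expected response rate.

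The section on cohort study 1 uses the same rule but starts from expected responders: "As we expect a response in about 65 of 70 centres, prediction models can include about 6-7 predictors at centre level". Near its end, the Discussion says of the whole study that "we need a high response rate to avoid selection of highly motivated researchers, patients and clinicians", without a figure.

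**The concern.** The calculation puts the sampling frame where the analysed sample belongs. A trial whose team does not return the questionnaire contributes no observed data on the surveyed predictors, such as who was responsible for recruitment or the group's training and experience. The article names no other source for these. Non-responding trials therefore cannot be counted towards the events that support the model.

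Cohort 1 shows that the authors regard response as part of this calculation; for cohort 2 it is left out. The sentence is cohort 2's only justification of size, and the cohort 2 model feeds the recommendations and checklist described in the Discussion. If the candidate list were built up to 30 on the strength of this sentence, the model could have fewer events per predictor than the plan's own rule asks for.

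**Working it through.** **Inputs.** From the cohort 2 section: N = 1000 available trials, success rate p = 0.30 (labelled low), 10 events per predictor. From the cohort 1 section: 65 of 70 centres expected to respond, 65/70 = 92.9%. All other response rates r, and the success rates of 40% and 50%, are assumptions chosen to show a range.

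**Reproducing the plan's figures.** Cohort 2: 1000 x 0.30 = 300 events; 300 / 10 = 30, as stated. Cohort 1: 65 / 10 = 6.5, matching the stated 6 to 7 after allowing for response.

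**Allowing for response in cohort 2.** Capacity = N x r x min(p, 1 - p) / 10, where p is the success rate among trials that reply. At p = 0.30 this is 30 x r. If 30 predictors were kept, events per predictor would be N x r x 0.30 / 30 = 10 x r.

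| Response | Events at 30% success | Capacity at 30% | Events per predictor if 30 kept | Capacity at 40% | Capacity at 50% |
|---|---|---|---|---|---|
| 100% | 300 | 30 | 10 | 40 | 50 |
| 92.9% (cohort 1) | 279 | 27.9 | 9.3 | 37.1 | 46.4 |
| 80% | 240 | 24 | 8 | 32 | 40 |
| 70% | 210 | 21 | 7 | 28 | 35 |
| 60% | 180 | 18 | 6 | 24 | 30 |
| 50% | 150 | 15 | 5 | 20 | 25 |

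**Response needed for 30 predictors.** Setting 1000 x r x min(p, 1 - p) / 10 = 30 gives r = 0.30 / min(p, 1 - p):
- p = 0.30: r = 100%
- p = 0.40: r = 75%
- p = 0.50: r = 60%

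Because min(p, 1 - p) cannot exceed 0.50, capacity cannot exceed 50 x r. Below 60% response it is under 30 whatever the success rate.

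**Can a larger mailing make up the loss?** At 30% success, 300 events require 1000 returned questionnaires. That means approaching 1000 / 0.80 = 1250 trials at 80% response, or 1000 / 0.50 = 2000 at 50%. About 1000 are available.

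**The case against.** The case on the other side is substantial, and most of it limits the size of the point rather than removing it.

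- *The arithmetic is right and the sentence is conditional on a sample of 1000.* Both are true. But the only 1000 in the article is the count of available trials, so the condition amounts to full response.
- *The 30% is described as low, so there may be headroom.* This stands. The Background reports that fewer than a third of a UK cohort reached their full target on time, and cohort 2's 80% criterion is easier to meet. A higher success rate would offset some non-response. The article does not make this argument, and the offset runs out below 60% response.
- *The plan never commits to 30 candidates.* This also stands. The section names about eight or nine predictors. At 30% success, nine need 9 x 10 / 0.30 = 300 returned questionnaires, or 30% response.
- *Bootstrapping, shrinkage and a fallback to risk-factor identification are planned.* They are, and they temper overfitting. They do not make the stated capacity consistent with the plan's own rule.
- *Missing data are covered:* "Missing values will be imputed. Like in the cohort study I, the predictive accuracy of the model will be assessed using calibration". The text does not tie imputation to unreturned questionnaires, and imputing a whole questionnaire adds no observed predictor data.

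A reader might infer that cohort 2 will fit 30 candidates on perhaps half the required events, and that its checklist will be unreliable as a result. The documents do not support that. They give no cohort 2 response rate, do not propose a 30-candidate model, and do specify overfitting safeguards.

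**Conclusion.** The point holds as a wrong denominator in a stated capacity figure, not as a calculation error and not as proof that the model will be overfitted. At the plan's own 30% success rate, 30 predictors require a usable questionnaire from every available trial, and the article says nothing to justify that while allowing for response in cohort 1.

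The size depends on a response rate the documents do not give. At cohort 1's 93% the loss is about two predictors, which is small against a figure given as approximate. At 70% it is nine, and at 50% half the stated capacity is gone. These figures assume 30% success among responders. The statement that no success rate rescues 30 below 60% response also assumes that the rarer outcome is the one counted as the event, which is how the plan's 30% enters its own calculation.

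The sentence should be corrected. It does not invalidate cohort 2, since the predictors actually named would fit within a much lower response.

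**What to change.** In the cohort 2 section, replace the capacity sentence with one based on expected usable questionnaires x the rarer outcome's rate / 10, and state the expected response rate, which the authors must supply. For illustration, at 30% success this gives about 21 predictors at 70% response and about 15 at 50%. Alternatively, keep 30 and state the minimum response it requires: 100% at 30% success, 75% at 40%, 60% at 50%.

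Add that the number of candidate predictors will be capped at the resulting budget once the number of returns is known and before any predictor-outcome association is examined.

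The cost is a change of wording and a less favourable stated number of predictors. No additional data collection is needed.

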## Discussion

At the end of the study, we will have an inventory of predictors, barriers and facilitators for successful patient recruitment in trials. The first cohort study will provide information on prediction of recruitment in different centres participating in obstetrical, subfertility and gynaecological trials. From the nested case-control study we will obtain qualitative and quantitative information about factors which influence patient participation. The second cohort study will provide insight in factors related to successful recruitment at study level. Based on the prediction models or risk factors for unsuccessful recruitment, we will develop a set of recommendations and a checklist that can be used by individual trialists before the start of the study to assess if recruitment of the proposed sample size with their strategy will be feasible.

A strong point of the design is that we will address recruitment factors at different levels and from different perspectives, throughout a variety of trials in various fields of medicine. This will provide us with a broad overall picture of reasons why patients participate or refuse participation, and will provide insight in a common denominator between trials, or clarify differences. At the same time this is a potential pitfall: the reasons for participation or non-participation in a clinical trial might predominantly depend on exclusive characteristics of a trial and its targeted population, so that general predictors may not be identified. If so, the results are still valuable, but we should focus on the development of a general applicable recruitment tool. Such a tool might consist of a strategy based on interviewing a number of eligible participants as well as a number of recruiters and/or clinicians prior to start or during the piloting of the trial.

Another strong point is that the first cohort is based on clinicians recruiting for a set of trials from the nationwide consortium in Obstetrics and Gynaecology. All academic medical centres and the majority of the Dutch hospitals recruit for trials running in this consortium, which enables us to cover a large part of the Netherlands without selection of the explicitly research minded hospitals. Moreover, the second cohort of studies from the Dutch Trial Register will be a representative sample of all trials performed in the Netherlands, since from July 2005 registration is required for publication in important journals. It will be a challenge to deliberately handle the heterogeneity of the trials included.

There are also some limitations in this study which require a remark. First, although we focus on different levels (level of the patient, centre and study) it is not possible to directly link the data from these levels. We therefore cannot disentangle the relative impact of each level to the recruitment problems. However, we will be able to provide a satisfactory estimation, given the variability between different specialties and trials.

Second, as we focus on trials in obstetrics and gynaecology in the first cohort study, generalisability of these results to other clinical specialties should be evaluated. As in this study it is not feasible to survey all specialties in depth, we think it is more informative to have a complete picture of one specialty over a limited amount of information from many specialties.

Furthermore, in the second cohort on predicting successful recruitment on study level, the predefined recruitment target will probably - as most power calculations - be based on limited information. When information emerges from external sources or interim analyses, the sample size might be adapted, which can make the trial more successful or efficient without reaching the originally planned sample size. However, sample size targets are taken into account when funding decisions are made. The extent to which a trial meets initial expectations can be viewed as a legitimate marker of trial success. Moreover, recruitment can be viewed of as a surrogate marker of more significant markers of success, such as the extent to which the trial question has been successfully addressed [1].

Interviewing patients from different specialties and trials will provide a broad spectrum of why patients participate or refuse. This will limit the number of patients interviewed from one trial, but the quantification of these reasons in a representative group of patients will allow us to examine differences between these specialties and trials.

Finally, as this study will be performed in the Netherlands, the Dutch health care system as well as the position of medical research in the Netherlands might influence its results. Existing literature can be used to compare our results with those from other countries. We realize that especially to make this study a success we need a high response rate to avoid selection of highly motivated researchers, patients and clinicians.

In conclusion, this design allows us to identify determinants for unsuccessful recruitment. Identified predictors for unsuccessful recruitment can be coupled to evidence-based strategies to improve recruitment in trials [7].
